Research on RTW in cancer survivors has in recent years increased, partly because survival rates have increased [18, 19], and because patients with advanced, incurable disease are able to perform some kind of work, and will often prefer to stay on the labour marked as long as possible. Nevertheless, there still is a need for rigorous studies applying a randomised controlled trial design, with thorough information on intervention components and data reporting [19]. Due to the inconsistent conclusions drawn from the existing RTW studies in cancer survivors; evidence from research conducted on musculoskeletal and/or mental-related sickness absentees can give insights into effective RTW interventions in general and guide researchers in putting hypotheses forward on which elements cancer-oriented RTW interventions may contain. Thus, the provision of occupational rehabilitation to cancer survivors that consists of a combination of general and cancer specific intervention elements may prove to be an effective approach.

Some evidence supports that RTW interventions targeted musculoskeletal-related [20] or depressed absentees [21] are more effective when they address the workplace than interventions not targeting the workplace. Thus, in the planning of the present study it was crucial to incorporate involvement of the workplace as one of the key elements in the intervention. In a cancer setting it has been shown that employer and colleague support as well as work accommodation increases the RTW rate and reduces the likelihood of cancer-related work impairments after RTW [13].

Problem-solving-therapy interventions towards employees sick-listed due to adjustment disorders enhanced partial RTW compared to a non-guideline based care [22]. Cancer survivors may also display adjustment disorders due to difficulties in coping with having a cancer diagnosis along with expectations from relatives and friends, workplace and health care professionals in the RTW process. Fear of cancer recurrence may lead to fear avoidance behaviour, which limits participation in life - including work [23, 24]. Therefore, the identification of cancer survivor-experienced barriers regarding RTW and assistance in barrier modification were important elements that the present intervention should include.

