### Participants

#### Intervention group

Cancer patients diagnosed with breast, colon-rectal, head and neck, thyroid gland, testicular, ovarian or cervix cancer referred to surgery, radiotherapy or chemotherapy at the Oncology Department at Aarhus University Hospital. Patients must be residents in the municipalities of Silkeborg or Randers, be at the age of 18–60 years and have a permanent or temporary employment (with at least 6 months left of their contract) at the inclusion date. Patients are eligible for participation whether they are still working or being on sick leave.

Patients, for whom the treating physician considers occupational rehabilitation to be unethical, or who are not reading or talking Danish are excluded.

Recruitment started in December 2013 and continues until the required sample size is obtained.

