#### Control group

The control group is defined by patients with identical inclusion and exclusion criteria as the intervention group except that they live in other municipalities than Silkeborg and Randers.

The control group is identified via the electronic patient records at the Aarhus University Hospital.

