### Recruitment of the intervention group participants

Patients are recruited to the intervention group in a three-stage process:At each cancer ward a nurse or assistant nurse assigned to this project identifies patients living in Randers or Silkeborg municipality with the eligible cancer diagnosis.The treating oncologist is notified of this patient and at first given consultation the patient is informed about the project, is handed a written information sheet also containing an informed written consent formula. The patient is asked to read the information sheet and is informed that a municipal job consultant will contact the patient at home by phone.The municipal job consultant may also identify eligible patients even before cancer treatment has begun because of sick leave spells exceeding 8 weeks. In that case the treating hospital ward is notified about inclusion status; in that way no cancer survivor is asked twice about inclusion.Finally the patient is telephoned by the municipal job consultant, who thoroughly informs the patient about the project. Participation includes the patients’ willingness to involve next of kin, employer, and colleagues. If the patient accepts participation the first meeting is set up and the informed written consent formula is signed on that occasion.

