### Statistical analyses

#### Primary outcome

The cumulative incidence proportion (CIP) as a function of the number of follow-up weeks is estimated using the Kaplan-Meier curve. The relative cumulative incidence of RTW within 52 weeks will be analyzed in a generalised linear regression model using the pseudo values method [63, 64].

Entry time is defined as the end of cancer treatment (identified from the hospital records) and the end of follow-up is 52 weeks following entry time. The outcome variable RTW consists of two measures: an event indicator (yes or no) and the time until RTW is identified in the DREAM register [65] or end of follow-up / competing risks (*early retirement benefit, retirement pension or death*)/censored observations (*emigration*), whichever comes first.

Adjustments for gender, age, cancer diagnosis, time since diagnosis and Charlson’s co-morbidity index [58] are going to be carried out. Moreover, analyses of whether socio-economic status or Charlson’s co-morbidity index modifies the effect of the intervention on RTW will also be carried out.

The significance level is set at p < 0.05. The results will be shown as crude and adjusted relative cumulative incidences, i.e. risks (RR) and corresponding 95 % confidence intervals (95 % CI).

STATA version 13.1 will be used as statistical software.

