## Discussion

This controlled trial uses the existing setting by which occupational/vocational rehabilitation takes place in Danish municipalities as of today. Already job consultants are appointed the role as case managers in cases of long-term sickness absence. Sick leave due to cancer is however, dealt with in different ways compared to less serious conditions; partly because of taboo, reluctance of discussing work with a potentially fatally ill absentee and off cause due to compassion for this person. However, the social security system, i.e. the Sickness Benefit Act and whether the cancer survivor is entitled to receive sickness benefit may not differentiate between the reasons for sick leave. As a consequence the cancer survivor may lose financial security while being sick-listed and also lose her or his job in the long run [7, 26, 27]. Moreover, the cancer survivor is left on her or his own to deal with these challenges, despite the fact that the majority of cancer survivors are motivated for and wishes to RTW [11].

The innovative element of this intervention is the timing and early onset of the occupational rehabilitation which is much earlier than usual and that the job consultants are articulating work and take action on the cancer survivors’ R-RTW and support them in behaviour change towards RTW. The evaluation of this intervention will point out if this approach in deed increases the RTW chance compared to the control municipalities.

The intervention will also be evaluated through qualitative interviews in terms of its acceptability to stakeholders and whether the existing setting is appropriate and whether job consultants are capable of this task.

The knowledge of RTW facilitators and barriers are quite extensive [2]. However, in the present trial it was not possible for us to take into account all of these factors. The cancer-related symptoms and possible disabilities due to treatment are not addressed directly within our intervention protocol. As the intervention takes place parallel with cancer treatment all of the cancer survivors are in contact with the health care system. If the job consultants identify health-related barriers in relation to RTW, they are intended to suggest the cancer survivor to get in contact with the treating oncologist or the general practitioner (GP). As well as the job consultants themselves can contact the health care professionals for advice.

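### The fixed adjustment set for a non-randomised comparison omits cancer treatment modality, which diagnosis and time since diagnosis capture only in part

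*Protocol article*

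**What the plan says.** All references are to the protocol article.

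- **Model (Statistical analyses, Primary outcome).** The 52-week relative cumulative incidence of RTW is modelled with pseudo values. The covariates are listed: "Adjustments for gender, age, cancer diagnosis, time since diagnosis and" the Charlson index. Neither treatment modality nor treatment intent appears in the analysis section.
- **Time origin (same section).** "Entry time is defined as the end of cancer treatment (identified from the hospital records". Hospital records are therefore consulted for every analysed patient.
- **Eligibility (Participants, Intervention group).** Patients with any of seven diagnosis groups who are "referred to surgery, radiotherapy or chemotherapy at the Oncology Department at Aarhus University Hospital" may enter.
- **Allocation (Participants, Control group).** Controls meet the same criteria "except that they live in other municipalities than Silkeborg and Randers". There is no randomisation.
- **Assembly of the groups.** For controls: "The control group is identified via the electronic patient records at the Aarhus University Hospital". Intervention patients are found by ward staff and informed by the oncologist, or found by a job consultant, who "may also identify eligible patients even before cancer treatment has begun because of sick leave spells exceeding 8 weeks". They must then consent and be willing to involve their employer (Recruitment of the intervention group participants). The sample size section expects 80% to consent.
- **Acknowledged confounding (Methodological considerations).** Residual confounding is mentioned only in connection with the choice of control municipalities.

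**The concern.** Without randomisation, the covariate list is the main protection against differences in case mix. The Background treats side effects of cancer treatment, symptoms and function as factors in RTW, so the treatment a patient faces is a plausible predictor of the outcome. Within one diagnosis, one patient may have surgery alone and another surgery followed by chemotherapy and radiotherapy.

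If the two recruitment routes select differently on this, the difference passes into the relative risk. Identification through long sick-leave spells, consent, and the physician's judgement that rehabilitation would be unethical could each do so. The article does not say how that last criterion is applied to controls found from records.

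The list is stated explicitly rather than left open, and the analyst is not blinded. A treatment term added after the data are seen would be open to the charge of post hoc choice.

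**Working it through.** **1. The plan's own figures.** The sample size section gives RTW of 82% and 60%, 10% mortality, 250 RTW events for the adjusted analyses, and 430 patients of whom 90 are in the intervention municipalities (so 430 − 90 = 340 controls).

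- Intervention share: 90/430 = 0.209.
- Overall RTW probability: 0.209 × 0.82 + 0.791 × 0.60 = 0.646.
- 250/0.646 = 387, and 387/0.90 = 430. The stated total reproduces.
- Planned relative risk: 0.82/0.60 = 1.37.

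None of these figures depends on the covariate list.

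**2. Possible bias from leaving modality out.** The documents give no RTW rates by treatment and no treatment mix by municipality. Both inputs are therefore assumptions:

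- difference between groups in the share on chemotherapy, within diagnosis: 0.05 to 0.15;
- difference in 52-week RTW between patients with and without chemotherapy: 0.15 to 0.25.

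Bias in the RTW difference = imbalance × RTW gap:

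- low end: 0.05 × 0.15 = 0.0075;
- high end: 0.15 × 0.25 = 0.0375.

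Apparent relative risk when the true one is 1, at 60% control RTW:

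- low end: (0.60 + 0.0075)/0.60 = 1.01;
- high end: (0.60 + 0.0375)/0.60 = 1.06;
- with the imbalance reversed: 0.5925/0.60 = 0.99 and 0.5625/0.60 = 0.94.

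**3. Sensitivity to wider assumptions.** For a binary factor with RTW ratio R and prevalence p1 (intervention) and p0 (control), the bias factor is (p1·R + 1 − p1)/(p0·R + 1 − p0).

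| R | p1 v p0 | Bias factor |
|---|---|---|
| 0.9 | 45% v 55% | 0.955/0.945 = 1.01 |
| 0.7 | 40% v 60% | 0.88/0.82 = 1.07 |
| 0.5 | 40% v 60% | 0.80/0.70 = 1.14 |

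The last two rows need a 20-point imbalance and are given only to show how the result moves.

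**4. Effect on the test.** Take 90 v 340 patients, 60% control RTW and no true effect. A simple comparison of proportions has standard error √(p1(1 − p1)/90 + 0.24/340). A bias factor of 1.05 raises the false rejection rate from 5% to about 8%. At the high end of step 2, p1 = 0.6375, the standard error is 0.0572 and 0.0375/0.0572 = 0.66, so the rate is Φ(0.66 − 1.96) + Φ(−0.66 − 1.96), about 10%. At the low end it stays at about 5%.

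**5. How plausible the imbalance is.** By chance alone, the difference in a factor with 50% prevalence has standard error √(0.25 × (1/90 + 1/340)) = 0.059. Five points is thus within ordinary chance variation. Fifteen points is about 2.5 standard errors (0.15/0.059) and would normally need systematic selection.

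**6. Room in the model.** Assume one term each for gender, age, time since diagnosis, Charlson index and group, plus six for seven diagnosis groups: 11 parameters, or 250/11 = 23 events per parameter. A three-level modality adds two: 250/13 = 19. Adding intent as well: 250/14 = 18.

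**The case against.** Several features limit the problem.

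- **Partial proxies are in the model.** Follow-up starts at the end of treatment. If time since diagnosis is measured at that point (the natural reading, though not stated), it is the interval from diagnosis to end of treatment and tracks treatment length. A reader might infer that the model ignores treatment altogether; with diagnosis and this interval included, it does not. The proxies still do not separate modalities within a diagnosis.
- **One hospital, national standards.** Both groups are treated at the same hospital, and the Background describes national clinical standards for cancer treatment. Treatment choice within a diagnosis should depend little on municipality. This stands as a reason to expect modest imbalance. It does not remove selection through consent or job-consultant identification. The abstract's statement on social inequality concerns social groups and shows no difference between municipalities.
- **Intent is weakly supported.** A reader might infer from "patients with advanced, incurable disease are able to perform some kind of work" that non-curative patients are a known source of confounding here. That sentence is general background on RTW research. Physicians may exclude patients for whom rehabilitation would be unethical, and follow-up needs an end of treatment, so few such patients may remain.
- **The Discussion does not concede the point.** "The cancer-related symptoms and possible disabilities due to treatment are not addressed directly within our intervention protocol" might be read as an admission about the analysis. It describes what the job consultants deliver and neither supports nor excuses the covariate list.
- **Strength is not documented.** The documents support treatment effects as an RTW factor only qualitatively, so calling modality a strong determinant goes beyond them.

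What remains is that the list is explicit, modality is not on it, and the groups are assembled by different routes.

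**Conclusion.** The point holds as a moderate, inexpensive improvement to the adjustment set. The plan contains no contradiction or arithmetic error here. Residual confounding by treatment modality is possible in either direction, and its size cannot be read from the documents. Under the stated assumptions the null relative risk lies at about 1.01 to 1.06, or 0.94 to 0.99 with the imbalance reversed. On the log scale the upper end is 0.06 against ln(1.37) = 0.31 for the planned effect, about one fifth; the lower end is negligible. These figures rest wholly on the assumed imbalance and RTW gap, with nothing absorbed by time since diagnosis. They do not show that the trial's estimate will be biased. Any precision gained by including modality is not quantified.

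**What to change.** In Statistical analyses, Primary outcome, add treatment modality to the pre-specified adjustment set, for example as surgery only, radiotherapy without chemotherapy, or any chemotherapy.

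- **Timing.** Use the treatment planned at inclusion or at first referral, with one anchor that can be found in both groups. The treatment actually received by the end-of-treatment date is known only after enrolment and could in principle be affected by the intervention.
- **Source.** Extract it by the same rule in both groups from the hospital records already read for the end-of-treatment date. Eligibility is itself worded in terms of referral to a modality.
- **Reporting.** Tabulate modality by group.
- **Intent.** Treatment intent at the same time point may be tabulated, and added to the model if enough non-curative patients enter the analysis.

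The cost is one or two abstracted fields per patient and two or three parameters, leaving about 18 to 19 events per parameter with 250 RTW events. Two limits remain: planned treatment will miss later changes, and the any-chemotherapy level pools chemotherapy alone with combined treatment.

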## Abstract

**Background:**

Cancer survivors are often left on their own to deal with the challenges of resuming work during or after cancer treatment, mainly due to unclear agreements between stakeholders responsible for occupational rehabilitation. Social inequality exists in cancer risk, survival probability and continues with regard to the chance of being able to return to work.

The **aim** is to apply an early, individually tailored occupational rehabilitation intervention to cancer survivors in two municipalities parallel with cancer treatment focusing on enhancing readiness for return to work.

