Feuerstein et al. developed the Work and Cancer Model based on an extensive review of the literature [25]. A variety of factors coexists and may act both as facilitators and inhibitors of RTW among cancer survivors; individual characteristics, health and well-being, symptoms, function, work demands, work environment and finally structural factors [25]. There seems to be agreement in the literature that RTW-interventions in general should target the multi-dimensional factors that are associated with sickness absence and that seems also to be true in a cancer specific context. This perspective is in part substantiated in the Cochrane review by de Boer et al. on RTW interventions to cancer survivors. Although the studies had low quality it was concluded that one-dimensional interventions, i.e. psychological, physical or medical interventions did not improve RTW compared to care as usual, whereas a moderate quality evidence was found for a multidisciplinary approach (involving physical, psychological and vocational elements) compared to care as usual [18].

Cancer survivors in low socioeconomic groups may in particular experience the RTW-process difficult and tend to be at risk of recurrent sickness absence, unemployment or permanent withdrawal from the labour market [7, 26, 27]. It is not clear which role socioeconomic status plays on cancer survivors’ RTW-process, but unfavourable work conditions characteristic for low income and low-level educational jobs may explain some of this inequality [28]. Therefore work accommodations and supervisor support may be of particular importance in occupational rehabilitation in cancer survivors [3, 10, 29] to help cancer survivors overcome the imbalance between health and work demands.

Despite improved long-term survival rates for cancer patients, survivorship does not mean living without health complaints, but rather living with a chronic disease [30]. Cancer survivors do have an increased risk of recurrent cancers along with co-morbidities like cardiovascular disease, diabetes, osteoporoses etc. [31]. This further increases the risk for reductions in workability and calls for collaboration between the occupational rehabilitation stakeholders to enhance the chance of sustainable RTW.

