#### Secondary

The secondary outcomes are whether socioeconomic status or co-morbidity is modifying the effect of the intervention on RTW.

Socioeconomic status is defined by type of work, educational level and last year household income before taxes, which are collected from Statistics Denmark [57].

Co-morbidity is defined by the Charlson-index; a weighted index including the number and seriousness of co-morbid diseases [58]. Data on diagnosis used in the Charlson-index are collected from the National Patient Registry in Denmark [59].

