### Methodological considerations

The golden standard when effects of an intervention are to be assessed is the randomised controlled trial (RCT) [18]. However, when studies are conducted in real settings, like in municipal job centres; recently published articles from the Danish national return-to-work program showed challenges in applying a randomised study design; i.e. spill over effects between study arms within the municipality [67–69]. Therefore we chose a controlled study design. When the control municipalities are to be chosen, high priority will be given to municipalities that resemble the RTW rate of the intervention municipalities the year before our study was initiated, i.e. 2013. For that purpose official rates from Statistics Denmark [57] will be used. We may not be able to identify municipalities which also can supply sufficient numbers of cancer patients fulfilling the inclusion and exclusion criteria. We might need to compromise on which municipalities to include as controls to get sufficient numbers of cancer survivors, which in turn might give residual confounding that will lower the internal validity of our results.

We believe that if the job consultants are to succeed in their support and help to the cancer survivors and thereby increase the R-RTW; they must identify barriers and facilitators in the RTW process and use the ACT inspired dialogue. Otherwise they may not be able to engage the cancer survivors in committed actions that are value-based and make sense to the survivors’ perception of quality of life (including work). In order for us to keep track of the compliance with the study protocol; the job consultants attend monthly supervisions with the psychologist who trained them in the use of ACT and IPS. Because the intervention takes place in the job consultants usual work setting, we fear that they are at risk of resuming old work habits and thereby violate the innovative elements in our intervention. We anticipate that the supervisions act as an arena where experiences are shared and difficult situations are discussed in order for the job consultants to learn and cope with their new job tasks and demands.

Due to the described intervention given by the job consultants it is not possible to blind the cancer survivors nor the job consultants or the person who will perform the analyses.

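### The stated adjustment set for the primary return-to-work analysis omits socioeconomic status, which may confound a non-randomised comparison of municipalities and is already due to be obtained

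*Protocol article*

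**What the plan says.** All references are to the protocol article.

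- **Adjustment set** (Statistical analyses, Primary outcome): "Adjustments for gender, age, cancer diagnosis, time since diagnosis and" Charlson's index. The next sentence begins "Moreover, analyses of whether socio-economic status or" and names Charlson again, this time as a candidate modifier. Crude and adjusted RRs are both to be reported.
- **SES data** (Outcomes, Secondary): "Socioeconomic status is defined by type of work, educational level and last year household income before taxes, which are collected from Statistics Denmark".
- **SES and the outcome:** the abstract states "Social inequality exists in cancer risk, survival probability and continues with regard to the chance of being able to return to work". The Background (Cancer and return to work) says "Cancer survivors in low socioeconomic groups may in particular experience the RTW-process difficult" and mentions the risk of renewed absence, unemployment or leaving the labour market. It then adds a qualifier: "It is not clear which role socioeconomic status plays on cancer survivors’ RTW-process".
- **Design:** the control group meets the same criteria but lives in other municipalities (Participants, Control group). Methodological considerations explains why randomisation was not used: "Therefore we chose a controlled study design". Control municipalities with a 2013 RTW rate like that of the intervention municipalities get priority. The authors may have to relax this to reach the numbers, and they concede that residual confounding could follow.

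**The concern.** Without randomisation, the adjusted RR depends on which baseline differences the model accounts for. SES is a natural candidate. The article associates it with RTW, it is fixed before the intervention starts (so it is not a mediator), and where people live is a plausible source of SES differences. Recruitment could add to this: intervention participants must agree to the involvement of employer and colleagues, while controls are identified from patient records.

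The planned modifier role does not explain the omission, since Charlson is both a modifier and an adjustment variable. Nor does the modification analysis fill the gap: it gives effects within SES strata and leaves the primary RR unadjusted for SES. If SES does differ between groups, the primary RR is shifted by an amount that its confidence interval does not show.

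**Working it through.** **1. The plan's own figures.** Inputs from Sample size calculation: RTW 82% and 60%, 20% of patients in the intervention municipalities, 10% mortality, 90% power, 5% significance level (taken as two-sided).

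- HR = ln(0.18)/ln(0.40) = 1.87. The ratio is printed the other way up, which would give 0.534; the value used is 1.87.
- Events (Schoenfeld) = (1.960 + 1.282)² / (0.2 × 0.8 × ln(1.87)²) = 168.
- Mean RTW share = 0.2 × 0.82 + 0.8 × 0.60 = 0.644. N = 168/0.644/0.9 = 289.9, matching 290.
- With 90 intervention and 340 control patients: 90 × 0.9 × 0.82 + 340 × 0.9 × 0.60 = 66.4 + 183.6 = 250 RTW events, matching the 250 sought for the adjusted analyses.

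The sample size reproduces and does not bear on the concern, except for feasibility (step 4).

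**2. Possible size of confounding (all SES inputs assumed).** Treat SES as low or higher, hold control RTW at 60%, and assume no intervention effect.

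*Ratio form.* Assume 40% low SES in controls, a higher-to-lower RTW ratio k of 1.1 to 1.5, and d = 5 to 20 points fewer low-SES patients in the intervention group. RTW in the higher stratum is h = 0.60/(0.60 + 0.40/k). Intervention RTW is h × [(0.60 + d) + (0.40 − d)/k].

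| k | d | h | Intervention RTW | Spurious RR |
|---|---|---|---|---|
| 1.1 | 0.05 | 0.623 | 0.603 | 1.005 |
| 1.25 | 0.10 | 0.652 | 0.613 | 1.022 |
| 1.5 | 0.20 | 0.692 | 0.646 | 1.077 |

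This is 0.3 to 4.6 percentage points, or 1% to 21% of the planned 22-point difference.

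*Difference form.* Bias = (difference in low-SES share) × (RTW difference between SES levels).
- 0.10 × 0.15 = 1.5 points, so RR = 0.615/0.60 = 1.025.
- 0.20 × 0.25 = 5 points, so RR = 0.65/0.60 = 1.083.

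If the intervention group has more low-SES patients instead, the RR falls below 1 by a similar amount.

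**3. Against sampling error.** Take 60% RTW in both groups and 81 versus 306 patients (90 and 340 less 10%). In a simple binomial approximation, SE(ln RR) = √[(0.40/0.60) × (1/81 + 1/306)] = 0.102.
- Top of the range: ln(1.083)/0.102 = 0.78 SE, which would raise a two-sided 5% false-positive rate to about 12%.
- Bottom of the range: ln(1.005)/0.102 = 0.05 SE, which leaves it at about 5%.

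**4. Can the model carry SES?** Parameters in the listed model: group 1, gender 1, age 1, seven diagnoses 6, time since diagnosis 1, Charlson 1, total 11. 250/11 = 22.7 events per parameter. Coding the three SES variables with 3 to 9 parameters (assumed) gives 14 to 20 in total: 250/14 = 17.9 down to 250/20 = 12.5.

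**The case against.** The strongest reply is that confounding has not been shown. A predictor of RTW confounds only if it also differs between groups, and nothing in the article gives SES by municipality or group. The authors also built in some protection: the same age, employment, diagnosis and hospital criteria for both groups, and priority to control municipalities with a similar RTW rate, which may absorb part of any SES effect. They acknowledge residual confounding openly. All of this stands. It limits the claim to possible confounding, but gives no reason to leave SES out: similar municipal RTW rates do not balance SES among eligible cancer patients, and the authors expect that they may have to compromise on those rates.

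Feasibility also has a limit. Only about 66 of the 250 events fall in the intervention group, and events per parameter is a rule of thumb. This argues for compact SES coding, not for omission.

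Several stronger readings are tempting but unsupported:

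- **That the primary RR is biased.** Neither the existence nor the direction of an imbalance can be read from the article.
- **That SES is a main cause of not returning to work.** The Background reports an association and calls the role of SES unclear.
- **That the adjusted model is the only protection.** Eligibility and the choice of municipalities give partial protection.
- **That SES is stated to be available for every participant.** This is an inference from the register source and from the modification analysis, which needs SES in both groups.
- **That prior sick-leave weeks and calendar period are also wrongly omitted.** The DREAM register is described only as the source of the outcome, and no pre-entry history is mentioned. The July 2014 and January 2015 benefit changes fall after recruitment began in December 2013, but they confound only if the groups differ in calendar time, and nothing says they do. The article also says that the benefit period may be unlimited for people with cancer.

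**Conclusion.** The point holds as a potential and avoidable source of confounding. The article fixes an adjustment set without SES, although it links SES to the outcome, plans to obtain it, and compares groups formed by residence.

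The size and sign are unknown. The range of about 1.005 to 1.08 for the RR under no effect, or the inverse, rests wholly on assumed SES imbalances and SES–RTW associations. At the top it is large enough to distort the test (about 0.8 SE); at the bottom it is negligible. Even at the top it is well below the planned RR of 1.37, so it could not by itself produce the anticipated effect. Given how little the change requires, SES should be in the model.

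**What to change.** - Add education, type of work and household income to the pre-specified adjusted primary model. Fix the income year so that it precedes treatment, and set the coding in advance, kept compact.
- Keep the SES and Charlson effect-modification analyses as planned.
- State that the adjusted RR is the main estimate and the crude RR supportive.
- Prior sick-leave weeks and calendar period are at most optional covariates for a sensitivity analysis.

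The cost is mainly wording: the SES variables are already to be obtained for the secondary analysis, and no change in sample size follows. Prior sick-leave weeks, if used, would need extra data preparation.
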